### Randomization

Patient allocation to the control or TTVDP group will result from a 1:1 randomization with variable block size within each study center using the electronic data capture (EDC) system *Syncrony™* (Version 2018.01.02, Syntactx Technologies, New York, NY, USA). The randomization feature of Syncrony EDC was designed to utilize a randomization table created by an independent biostatistician using SAS 9.4 (SAS Institute Inc., Cary, NC, USA) according to the requirements in the study protocol. To ensure allocation concealment, the next randomization is unknown to the study center until the time at which a patient has signed informed consent, unique patient-identifying information is entered into the EDC, and the randomization button is pressed by the coordinator.

### Masking

This is an open-label study during which neither patients nor investigators will be blinded to treatment arm, primary outcome, or secondary outcomes.

Diaphragmatic ultrasound studies will be performed to provide diaphragm muscle characteristics as secondary outcomes in a subset of the participating sites. The analysis will be centralized at a core ultrasound laboratory where ultrasound reviewers will be blinded to the treatment arm (single blind).

### Management of control patients

Patients randomized to the control group will not receive TTVDP and will continue to be treated with the standard of care for patients who have difficulty being weaned from MV according to the procedures in effect at the study sites. The patients will undergo a daily weaning readiness assessment which, if positive, will be followed by a protocol-specific VLT conducted without pressure support and without positive end-expiratory pressure [31].

In addition to routine tests performed according to each site’s procedures, the following assessments will be performed:Maximal inspiratory pressure (MIP) according to the “coached version” of the unidirectional valve method described by Marini et al. [32] and Caruso et al. [33]; identical measurement procedures and devices will be used at all centers; MIP will be measured at time of enrollment, prior to extubation, and optionally every 7 daysRapid shallow breathing index (RSBI), calculated as the ratio of respiratory rate to tidal volume in liters [34], as part of the daily protocol-specific VLT or, when impossible, under MV set to an assisted breathing modeSequential organ failure assessment (SOFA) score [35, 36] at the time of enrollment and every 72 h until removal of the TTVDPDiaphragmatic ultrasound measurements on day of randomization, every 3 days, and on the day of extubation, to measure diaphragm thickness and thickening fraction (TFdi) and maximal diaphragmatic excursion (EXdi) [37]; these imaging measurements will be conducted according to a protocol-specific procedure, and the designated study site staff members will have received training and be qualified to conduct these imaging studies; a blinded review of all diaphragmatic ultrasound images will be performed at a core laboratory.

### Management of treatment patients

Participants randomized to the diaphragm pacing group will receive TTVDP but will otherwise be managed exactly as the patients randomized to the control group.

### Intervention protocol

#### Device description

The temporary transvenous diaphragm pacing system (TTVDPS, Lungpacer Medical Incorporated, Burnaby, BC, Canada) comprises:The LIVE® Catheter, a sterile, size 9.5 French, single-use disposable catheter resembling a typical polyurethane central venous catheter, further comprising two arrays of electrodes targeting the left (proximal array) and right (distal array) phrenic nerves, a single fluid lumen, and a primary cable containing electrical leads which terminate at an electrical connectorA cart-mounted Lungpacer Control Unit (LCU) including a touch screen user interfaceAn intermediary cable connecting the primary cable and control unitA handheld controller used to deliver electrical impulses as set by the physician on the controller unit (Fig. 2).

**Fig. 2 Fig2:**
[figure not shown]
Schematic representation of the Lungpacer LIVE® Catheter system providing temporary transvenous phrenic stimulation for diaphragm pacing (*LCU* Lungpacer Control Unit). Credit to [name]

The pulses have an intensity of up to 13.5 mA and a duration of 200–300 μs; they can be delivered with a frequency of 4 Hz for the mapping procedure (see the next section) and 15 Hz for the diaphragm pacing therapy itself.

#### Diaphragm pacing therapy

In the treatment group, the LIVE® Catheter will be inserted in the left subclavian vein using the Seldinger technique. Correct positioning of the catheter will be verified per the standard of care in each institution. A mapping procedure will be conducted before each therapy session to ensure adequate capture of both phrenic nerves and to determine the stimulation thresholds at which visible or manually palpable diaphragm contractions appear in response to the electrical impulses. The intensity will then be increased up to the maximal level tolerated by the patient. Therapy sessions will consist of 4 sets of 10 stimulations manually administered by a trained team member. The stimulation sets will be separated by a brief rest period as needed. Three therapy sessions (totaling 120 stimulations) will be conducted daily (morning, afternoon, and evening, with no less than 3 h between sessions).

#### Discontinuation of therapy

The diaphragm pacing therapy sessions will be stopped when the physician determines that the patient has successfully passed the protocol-specific VLT and can be separated from the ventilator. If discontinuation of therapy occurs before the 30-day study completion, the LIVE® Catheter will not be removed until the patient has met the weaning success criterion (48 h off the ventilator).

### Outcomes

The primary efficacy endpoint is time to successful extubation with no reintubation within 48 h. In tracheotomized patients, the primary efficacy endpoint is time to successful 24-h separation from the ventilator with no reconnection within the following 48 h.

The primary statistical analysis will model the time to event of interest, i.e., successful weaning, in the presence of competing events which include death or withdrawal of life support. The endpoint is evaluated in a competing risks survival model. In addition, withdrawal of life support and cessation of weaning in the ICU with discharge from the ICU to a specialized weaning facility by day 30 will be reported.

The secondary efficacy endpoints are:Time to first successful VLT after randomizationDifference in MIP changes between study groups from randomization to successful weaning or on day 30, whichever comes firstDifference in changes in diaphragmatic thickness (centralized blinded ultrasound evaluation) between study groups from randomization to successful weaning or on day 30, whichever comes firstDifference in changes in diaphragm thickening fraction (centralized blinded ultrasound evaluation) between study groups from randomization to successful weaning or on day 30, whichever comes firstDaily measurement of RSBI.

The safety endpoints will include characterizing the adverse event profile and comparing the nature and frequency of adverse events in patients randomized to TTVDP vs. control (standard of care) treatment. This safety assessment and the study risk management plan are described in detail within the study protocol.

Of note, additional observational data points will be collected, including (but not limited to) time to extubation, time to reintubation, time to ICU discharge, time to hospital discharge, and 30-day mortality from randomization.

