### Strengths, limitations, and uncertainties

#### Masking

A sham design has not been retained for the RESCUE 2 study because of the risks inherent to central venous catheterization. Therefore, the RESCUE 2 protocol does not require the placement of a central line in a control patient if this is not decided by the clinicians in charge of this patient in the context of routine care. The study is therefore controlled but not blinded, with the ensuing requirement for caution when interpreting the data. To limit the corresponding risk of bias, precautions have been taken to minimize the risk of discrepancies between the treatment and the control groups, notably regarding the inclusion process (e.g., requirement for a standardized VLT before inclusion in the study). Also, ultrasound diaphragm measurements will be evaluated by blinded operators at a core laboratory, which will allow one to credibly assess the ability of TTVDP to restore diaphragmatic mass and contractility in the study population, irrespective of the main outcome. Of note, blinded trials of medical devices are the exception rather than the rule.

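### The primary outcome sets when MIP and diaphragm changes are compared, and the text schedules no day-30 MIP for patients never extubated

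*Protocol article*

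**What the plan says.** Under Outcomes, the MIP endpoint is the difference "in MIP changes between study groups from randomization to successful weaning or on day 30", whichever comes first. The thickness and thickening-fraction endpoints use the same end time.

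The measurements are listed under Management of control patients. For MIP: "MIP will be measured at time of enrollment, prior to extubation, and optionally" every 7 days. For ultrasound: "measurements on day of randomization, every 3 days, and on the day of extubation". The treatment arm follows the same schedule, since those patients "will otherwise be managed exactly as the patients randomized to the control group". Ultrasound provides "secondary outcomes in a subset of the participating sites" (Methods, Masking).

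Two other rules bear on timing. Pacing ends with the outcome: "The diaphragm pacing therapy sessions will be stopped when the physician determines that the patient has successfully passed the protocol-specific VLT" and can come off the ventilator (Discontinuation of therapy). And not every weaned patient is extubated: "In tracheotomized patients, the primary efficacy endpoint is time to successful 24-h separation from the ventilator" (Outcomes).

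The Discussion gives the ultrasound results a special role. Its Masking paragraph says that they are read by blinded operators, "which will allow one to credibly assess the ability of TTVDP to restore diaphragmatic mass and contractility", whatever the primary result. Generalizability of the expected results says that they will matter greatly if the trial is negative.

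**The concern.** There are two separate faults.

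**Time point (all three endpoints).** A weaned patient is assessed on the weaning day and an unweaned patient on day 30. Weaning is the event that the therapy is meant to bring forward. If it works, treated patients are assessed earlier on average and have had less time to recover. If patients also tend to wean on reaching some level of strength, those who wean look alike in both arms however fast they got there. A true effect on the muscle can then be hidden, and a difference can appear where the daily course is the same.

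**Schedule (MIP only).** The endpoint needs a day-30 MIP in patients not weaned. The text lists only an enrolment value, a pre-extubation value and an optional weekly one. Whether a post-baseline MIP exists would then depend on the outcome.

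At stake is the mechanistic reading of the trial. The stated power is 70% even for an effect that the protocol calls dramatic, so a non-significant primary result is quite possible. That is when the Discussion intends to turn to the ultrasound data.

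**Working it through.** **Inputs.** Population size: 44 per arm; control 50% weaned and 34% with a competing event; TTVDP 80% and 11%; horizon 30 days. Statistical analysis: two-sided 0.05. Assumption: constant cause-specific hazards.

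**1. The plan's own power.** Total hazard = -ln(1 - F - C)/30, split in the ratio F:C (F weaned, C competing).
- Control: -ln(0.16)/30 = 0.0611 per day; weaning share 0.50/0.84 gives 0.0364.
- TTVDP: -ln(0.09)/30 = 0.0803 per day; weaning share 0.80/0.91 gives 0.0706.
- Hazard ratio 0.0706/0.0364 = 1.94; weaning events 44 × 0.50 + 44 × 0.80 = 57.2.
- Power = Φ(½ × √57.2 × ln 1.94 - 1.96) = Φ(0.55) = 70.8%, against 70% stated. The figure reproduces, so these hazards are a fair reading of the planning case.

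**2. Assessment day.** Weaned patients count at their weaning day, patients with neither event at day 30, and patients with a competing event not at all.
- Mean weaning day among the weaned, 1/λ - 30·S/(1 - S), with λ the total hazard and S the share with neither event: control 16.37 - 5.71 = 10.7 (10.6 by simulation); TTVDP 12.46 - 2.97 = 9.5.
- Mean assessment day: control (0.50 × 10.66 + 0.16 × 30)/0.66 = 15.3; TTVDP (0.80 × 9.49 + 0.09 × 30)/0.89 = 11.6.
- Share assessed at day 30: 0.16/0.66 = 24% vs 0.09/0.89 = 10%.

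**3. What this can do to the contrast (illustrations; the slopes are assumed).**

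Same linear MIP gain per day in both arms, so no treatment effect on MIP:

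| Gain per day (units) | TTVDP minus control, weaning or day 30 | Weaned only |
|---|---|---|
| 0.2 | -0.8 | -0.2 |
| 0.5 | -1.9 | -0.6 |
| 1.0 | -3.8 | -1.2 |

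Weaning once MIP has risen by 10 units, mean daily gain 0.3 vs 0.6 (SD 0.4), no competing events: the gain at day 7 is 2.1 vs 4.2, but among the weaned it is 10.0 in both arms. At weaning or day 30 it is 4.7 vs 8.2, a difference of 3.5. Thirty days at those rates would give 0.3 × 30 = 9.0.

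**4. Patients with a required post-baseline MIP, on the text's schedule.** Taking weaning as the guarantee of a pre-extubation value: 44 × 0.50 = 22 control vs 44 × 0.80 = 35.2 TTVDP. None is assured in 22 vs 8.8. Of these, 15.0 vs 4.8 have a competing event and 7.0 vs 4.0 are unweaned at day 30 without one. The count is approximate in both directions: a failed extubation also yields a pre-extubation value, while for a tracheotomized patient the phrase has no clear meaning.

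**5. Would an early common day remove the problem?** Weaned by day 7: control 0.595 × (1 - e^(-0.428)) = 21%; TTVDP 0.879 × (1 - e^(-0.562)) = 38%. Still free of both events: 65% vs 57%. A common day removes the unequal exposure time but not outcome-driven missingness.

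**The case against.** The best defence is that status at liberation or day 30 is a legitimate quantity, and that an early fixed day has its own differential missingness, as step 5 shows. Among weaned patients alone, the mean assessment day differs by only about 1.2 days. The endpoints are secondary, and the article disclaims any aim of showing definitive superiority. The trade-off is real. But the Discussion wants evidence on the diaphragm that does not hang on the primary result, and an end time set by that result cannot supply it. No analysis model cures this while the definition stands.

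Several stronger readings are tempting and are not supported:
- A reader might infer that MIP is never measured in patients who do not wean. Enrolment MIP is required in all, failed extubations have a pre-extubation value, and weekly values may be taken.
- A reader might infer that a day-30 MIP is certainly absent. Fig. 1 covers assessments and its legend defines MIP, but it is not shown. The gap is established only for the text.
- A reader might extend the missing-value argument to ultrasound. Scans are required every 3 days, so there the fault is the time point.
- A reader might think that the Discussion leans on MIP in the same way. Both paragraphs speak of ultrasound.
- A reader might size the MIP selection by comparing the top 50% with the top 80% of one normal distribution: 0.350 - 0.798 = -0.45 SD. That assumes the gain determines weaning and is distributed alike in both arms, which under a common threshold would give equal weaning rates. It cannot be squared with 50% vs 80%.

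Handling of deaths and missing values may sit in the full protocol's statistical plan and is not counted as missing here.

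**Conclusion.** The point holds for the time definition of all three endpoints. If the therapy works as planned, the arms are assessed about 3.8 days apart on average (15.3 vs 11.6), and the contrast mixes effect with time on study. This rests on constant hazards and on leaving out patients with a competing event.

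The likely direction is against TTVDP or towards zero, provided the measures improve with time. If they were still falling, the exposure part would change sign. The document gives no rate of change, so the figures in step 3 illustrate the mechanism and do not estimate the bias.

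For MIP, the endpoint and the schedule in the text do not match, subject to Fig. 1. The size of that selection cannot be fixed from the document.

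This should be corrected, but it concerns secondary endpoints only. A reader might infer a threat to the main result; there is none, and the stated power reproduces.

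**What to change.** **Thickness and thickening fraction.** Make the main between-arm comparison longitudinal, using the scans already required every 3 days: a repeated-measures model with the baseline value as covariate and an arm-by-time term, with the contrast at one pre-specified common early day. Report change at weaning or day 30 as descriptive.

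**MIP.** Reconcile Outcomes with Management of control patients. Require the weekly value, now optional, while the patient is ventilated, and a day-30 value in patients not weaned. State what replaces the pre-extubation measurement in tracheotomized patients. Analyse as above. If Fig. 1 already lists a day-30 MIP, bring the text into line with it.

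**Cost.** A few more bedside MIP measurements and a change of wording; no new scans. Values after weaning or death will still be missing, and unequally (about 21% of controls and 38% of TTVDP patients weaned by day 7 under the planning hazards). The model then rests on a missing-at-random assumption, which is doubtful if weaning depends on current strength, so a sensitivity analysis to departures from it should be pre-specified. The article says that Revision F is already being amended, so the change can go in with that revision.

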### Recruitment capacity and consent

We have calculated a sample size of 88 patients randomized 1:1 with 44 patients anticipated in each group (see below), to be enrolled over 14 months. Before any study-related activities begin, each patient (or the patient’s legally authorized representative) will be provided details of the study by an investigator and asked if they are interested in participating in this study. If they agree they will be asked to sign the informed consent form. Participation is voluntary and does not affect standard treatment in any way. Study patients may decide to end their participation in the study at any time.

### Population size

The sample size needed to show a statistically significant difference between treatment depends on the proportion of patients successfully weaned and the proportion succumbing to a competing risk prior to successful weaning by day 30 (see the previous section “Outcomes”). Since TTVDP is a novel, first-of-its-kind therapy both in general and in the population of patients experiencing difficult weaning from MV, no estimates of the effect size or the competing events were available. Consequently, a sample of convenience was used to allow enrollment and randomization of up to 88 study patients (44 per arm).

Using a competing risks model with a log rank test (PASS 14, NCSS Statistical Software, LLC, Kaysville, UT, USA), this population size gives the study a 70% power to find a statistically significant difference in the event of a dramatically large treatment effect (i.e., approximately 50% of patients weaned with 34% experiencing one of the competing risks in the control group, vs. 80% weaned with 11% experiencing one of the competing risks in the TTVDP group).

As a result, the totality of evidence is expected to indicate a trend in favor of TTVDP (with an adverse event profile not significantly different between the groups) rather than to show definitive superiority.

Of note, Revision F of the protocol as described in this manuscript is being amended to account for a higher than expected number of withdrawals due to inability to insert the guidewire: the target size population will be brought from 88 to 110, with the possibility for sites to include two roll-in subjects for training purposes. Accordingly, the number of participating centers will be increased from 14 to 22.

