### Statistical analysis

After the database is audited and locked, the statistical analysis will be conducted by a statistician independent of the sponsor and the CRO. The statistical plan described in the study protocol includes details about handling missing data, assessing comparability of randomized groups, and evaluating the pooled data collected at the various centers.

The data from the study will only be analyzed once at the end of the study, and no formal statistical stopping rules allow for the early termination of this study.

The analysis groups include the (1) intent-to-treat (ITT) population, defined as all patients who were randomized with a study group defined by the randomization; (2) modified intent-to-treat (mITT) population, defined as the complete control group and a subset of the ITT therapy group with successful cannulation of the left subclavian vein; and (3) per protocol (PP) population, i.e., a subset of the mITT population defined as those patients who completed at least 75% of the protocol-required stimulations in at least one phrenic nerve. The sidedness of the phrenic nerve stimulation can change from left to right or can occur in both phrenic nerves.

Descriptive statistics for continuous variables will include the number of observations, mean, standard deviation, minimum, median, and maximum. Descriptive statistics for categorical variables will include the number and percent in each category out of the total number of observed responses. The *p* values will be considered statistically significant if the two-sided *p* value is ≤0.05 unless otherwise specified. When the arithmetic mean is found not to be an appropriate measure of central tendency, alternative statistics will be considered (e.g., median, interquartile range). When the distribution of a variable does not support the use of parametric statistics, nonparametric approaches or data transformations may be implemented. If data transformations are used, they will be specified in the final clinical study report.

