Regarding the primary efficacy endpoint (time to successful extubation without reintubation in the next 48 h), the null hypothesis states the cumulative incidence by day 30 for successful weaning is the same in patients randomized to treatment or control groups. The primary statistical analysis will be conducted on the mITT population and will model the time to the event of interest in the presence of competing events which include death and withdrawal of life support. In addition, cessation of weaning in the ICU with discharge from ICU to a specialized weaning facility will be evaluated. Patients who do not meet one of the endpoints by the end of their study follow-up will be censored at the time of study discontinuation or completion. The primary statistical model will utilize the cumulative incidence function. The event of interest, successful weaning, will be compared between randomized groups using Gray’s test. The probabilities will be summarized for successful weaning and each competing event for the duration of the study. The 95% confidence intervals will be provided for the probabilities at 30 days. In addition, descriptive statistics will be prepared by randomized group for the time to successful weaning in days.

All ITT patients will be included in the primary safety endpoint analysis. Fisher’s exact test will be used to compare the number of patients with an event or in a category of events out of the total number of patients randomized between groups as a tool to understand the adverse event profile associated with TTVDP compared to control.

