In this context, RESCUE 2 will test a technology that is completely novel and that will be used therapeutically for the first time. A major advantage of this approach is that, contrary to inspiratory muscle training, it does not require patient cooperation or motivation. The study will be larger in size than most of the studies that have previously attempted to demonstrate a benefit of a therapeutic approach in difficult-to-wean ICU patients. Because of the “first-of-its-kind” nature of the therapy, it was not possible to power the study according to previous data and a sample of convenience was chosen, which does constitute a methodological limitation. However, note that many published studies validating indicators predictive of weaning success or failure have been conducted in smaller or similar samples [34, 59, 60]. This suggests that a sample of this size should be sufficient to detect differences between success and failure among patients.

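### The stated 70% power is that of a log-rank test, not of the planned Gray's test, which has about 86% power under the same assumptions

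*Protocol article*

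**What the plan says.** The Population size section explains that no estimates of effect size or of competing events were available, so "a sample of convenience was used to allow enrollment and randomization of up to 88 study patients (44 per arm"). It then attaches a power figure to that number. The method is "Using a competing risks model with a log rank test" in PASS 14, and the result is that "this population size gives the study a 70% power to find a statistically significant difference in the event of a dramatically large treatment effect". The scenario is "approximately 50% of patients weaned with 34% experiencing one of the competing risks in the control group", against 80% weaned and 11% with a competing event under TTVDP. The next sentence draws a consequence: the trial is expected to show a trend in favour of TTVDP rather than definitive superiority.

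The Statistical analysis section defines a different comparison. The null hypothesis is equal cumulative incidence of successful weaning by day 30, and the analysis set is mITT, which keeps all controls but only those TTVDP patients whose left subclavian vein was cannulated. The section says "The event of interest, successful weaning, will be compared between randomized groups using" Gray's test. The general rule on significance is two-sided: "values will be considered statistically significant if the two-sided *p* value is ≤0.05 unless otherwise specified". No power is given for Gray's test.

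In the Discussion, the section placing the study among weaning trials notes that many predictor-validation studies used similar or smaller samples, and adds: "This suggests that a sample of this size should be sufficient to detect differences between success and failure among patients".

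**The concern.** With competing risks, a log-rank test that censors competing events compares cause-specific hazards of weaning, while Gray's test compares cumulative incidence. The two respond differently when treatment also changes the rate of competing events, and the planning scenario assumes a large change of that kind (34% to 11%). A power figure for one test cannot then be carried over to the other.

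The article gives only one power figure. If it describes a test other than the primary one, the reader does not know the power of the primary analysis or the difference it can detect. The expectation of a trend rather than superiority also follows directly from that figure.

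**Working it through.** **Inputs.** From Population size: 44 per arm; control 50% weaned and 34% competing, so 16% neither; TTVDP 80% and 11%, so 9% neither. From Statistical analysis: two-sided 0.05. From Study setting: 30 days of follow-up. Assumed, because the article does not say: constant hazards, censoring only at day 30, and all 44 per arm analysed unless noted.

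**1. Reproducing the 70%.** With constant hazards, the weaning hazard per 30 days is F_w/(F_w + F_c) × [−ln(1 − F_w − F_c)].

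- Control: 0.50/0.84 × [−ln 0.16] = 0.595 × 1.833 = 1.091
- TTVDP: 0.80/0.91 × [−ln 0.09] = 0.879 × 2.408 = 2.117
- Cause-specific hazard ratio: 2.117/1.091 = 1.941, ln = 0.663
- Expected weaning events: 44 × 0.50 + 44 × 0.80 = 57.2
- Schoenfeld power: Φ(√(57.2/4) × 0.663 − 1.96) = Φ(3.782 × 0.663 − 1.96) = Φ(0.547) = 70.8%

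Simulating the same test (20,000 trials) gives 69.5%, and Freedman's formula gives 67.7%. A one-sided test would give 80.6%, so the stated 70% fits a two-sided cause-specific log-rank test with all 88 patients analysed. The article says only that a log-rank test was used; the cause-specific type is inferred from this match.

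**2. The planned test on the same inputs.** The contrast in cumulative incidence at day 30, expressed as a subdistribution hazard ratio, is ln(0.20)/ln(0.50) = 2.32, with ln 0.842.

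- Schoenfeld approximation: Φ(3.782 × 0.842 − 1.96) = Φ(1.226) = 89.0%
- Freedman approximation: 85.3%
- Comparison of the day-30 proportions, 50% against 80%: 85.2%
- Simulated Gray's test (20,000 trials): 86.2%
- The same with Weibull-type timing, shape 0.7 and 1.5: 86.1% and 85.6%

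Constant cause-specific hazards do not give a constant subdistribution hazard ratio, so the simulation is the better guide: about 86%, with the approximations between 85% and 89%. Under the null the simulated rejection rates were 4.8% for both tests.

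**3. The analysis population.** The article gives no rate of failed cannulation, so this is a range. With 44 controls:

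| TTVDP patients in mITT | Gray's test | Cause-specific log-rank |
|---|---|---|
| 44 | 86% | 70% |
| 40 | 84% | 68% |
| 37 | 83% | 67% |
| 35 (about 20% lost) | about 82% | 66% |
| 33 | 81% | 64% |

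**4. Other effect sizes, Gray's test, 44 per arm, control 50/34.** The competing-event rates under TTVDP here are assumed.

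| TTVDP weaned / competing | Power |
|---|---|
| 80% / 11% | about 86% |
| 76% / 14% | about 73% |
| 75% / 15% | about 68 to 70% |
| 65% / 22% | about 30% |

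**5. Direction of the gap.** The log-rank figure is lower here because TTVDP is assumed both to raise weaning and to reduce competing events; the second change widens the cumulative-incidence contrast (2.32 against 1.94). If competing events stayed at 34% and weaning rose from 50% to 62% (an illustration, not a scenario in the article), the order reverses: about 62% for log-rank and about 28% for Gray's test.

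**The case against.** The case for leaving the text alone is substantial. The article names the test behind its 70%, and for that test the figure is right. The sample size was not derived from it: 88 is declared a convenience sample, and the Discussion lists this as a limitation. At the stated effect the planned test has more power than claimed, so no one is misled into thinking the trial stronger than it is. The assumed loss of 20% of the TTVDP arm leaves power above 70%. Gray's test still needs a gain of about 25 percentage points for 70% power, so the message that only a large effect is detectable survives. The article also discloses the guidewire failures and the planned increase to 110.

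All of this stands, and it limits the point. A reader might infer that the 70% is an arithmetic error, or that the sample size is undermined; the documents support neither. Power at 110 belongs to an amendment that the article describes as still in progress, so its absence here is not a fault of Revision F.

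What the objection does not answer is that the article states both the power and the primary test, and they do not match. Nor can the gap be treated as safe in general, since its direction depends on the assumed effect on competing events.

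**Conclusion.** The point holds as a mismatch between the power calculation and the primary analysis. The 70% matches a cause-specific log-rank test; the planned Gray's test has about 86% power on the same inputs, a gap of about 16 percentage points, or about 82% power if 20% of the TTVDP arm leaves the mITT set. These figures rest on constant hazards (varying the shape moved them by less than one point), no censoring before day 30, and a cannulation-failure rate that the article does not give. The mITT figures also assume that excluding failed cannulations leaves the event rates unchanged.

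The consequence is for interpretation. At the effect the article calls dramatic, the planned test would be expected to reach significance in most trials, so the expectation of a mere trend does not follow from that scenario. It follows better from the possibility of a moderate effect: at 65% against 50%, power is only about 30%. A reader should not turn the 86% into a claim that the trial is well powered, because it applies only if TTVDP has both of the large effects assumed.

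The Discussion sentence on predictor-validation studies is a separate and minor matter. Those studies compare patients who succeed with patients who fail; their size says nothing about power to compare randomized arms, and the sentence sits badly with the expectation of only a trend.

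**What to change.** In the Population size section:

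- Restate power for Gray's test in the mITT population, two-sided 0.05, giving the assumed timing of events, censoring and cannulation-failure rate. Alternatively, keep the 70%, label it as the power of a cause-specific log-rank test (once the sponsor confirms from the PASS output that it is), and add the Gray figure beside it.
- Give the day-30 difference detectable at 70% and 80% power, with the competing-event rates assumed. By this check, 70% is reached at about 75% against 50% weaned, and power is about 30% at 65% against 50%.
- Rewrite the sentence expecting a trend so that it rests on the convenience sample and the unknown effect size rather than on the 70%.

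Separately, delete the Discussion sentence that infers adequate size from predictor-validation studies.

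The cost is one recalculation and a few sentences. The design, the primary test and the number of patients are unchanged.
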